**Comorbid pathology and general mental state measures**											
Diagnostic short-interview for mental disorders^c^^,^^I^	(50)	Diagnosis of comorbid symptoms (DSM-5)	–	–	Criterion fulfilled yes/partially/no	0.84–1.0		x			
Rating of negative EMOTIONS^Q^^,^^Post−session^	(51)	Arousal, anger, anxiety, sadness, disgust, stress, insecurity	7	–	5-point Likert scale from 0 (*not at all*) to 4 (*extremely*)	0.82–0.94		x		x	x
Questionnaire for social anxiety and social competence deficits for adolescents^d^^,^^Q^	(52)	Social anxiety and social competence deficiencies	44	Fear of talking and fear of being in the focus of attention; Fear of rejection; Interaction deficits; Information-processing deficits; Loneliness (additional subscale not counting for the total score)	4-point Likert scale from 0 (*never*) to 3 (*always/most of the time*)	0.76–0.90		x		x	x
Eating disorder examination questionnaire EDE-Q8	(53)	Eating disorder pathology	8	–	7-point Likert from 0 (*no day/never/not at all*) to 6 (*every day/every time/very much*)	0.93		x		x	x
Single Item Self Esteem Scale^Q^	(54, 55)	Self-esteem	1	–	7-point Likert scale from 0 (*not very true for me*) to 6 (*very true form me*)	–		x		x	x
Generalized self-efficacy scale^Q^	(56, 57)	Self-efficacy	10	–	4-point Likert scale from 0 (*not true*) to 3 (*exactly true*)	0.80–0.90		x		x	x
Multidimensional self-concept scale^Q^	(58, 59)	Estimation of self-esteem	32	Emotional self-esteem; Social self-esteem; Performance-related self-esteem; Body-related self-esteem	7-point Likert scale from 1 (*not at all/never*) to 7 (*very/always*)	0.76–0.87		x		x	x
Obsessive compulsive inventory-revised^Q^	(60, 61)	Symptoms of obsessive-compulsive disorder	18	Checking; ordering; hoarding; obsessing; washing; neutralizing	5-point Likert scale from 0 (*not at all*) to 4 (*very strong*)	0.85		x		x	x
Generic quality of life instrument for children -revised^e^^,^^Q^	(62)	Health-related life quality	24	Physical well-being, Psychological well-being; Self-esteem, Family; Friends; Education/school	5-point Likert scale from 0 (*never*) to 4 (*always*)	0.84		x		x	x
Rumination-suppression-questionnaire^f^^,^^Q^	(63)	Rumination/suppression as emotion regulation strategies	8	Rumination; Suppression	6-point Likert scale from 0 (*not at all true*) to 5 (*exactly true*)	0.50–0.83		x		x	x
Patient health questionnaire^Q^^,^^Post−module^	(64, 65)	Depressive mood	9	–	4-point Likert scale from 0 (*not at all*) to 3 (*nearly every day*)	0.86–0.89		x		x	x
Item on suicidal thoughts and plans, beck-depression-inventory-II^Q^^,^^Post−session^	(66, 67)	Suicidal thoughts and plans	1	–	4-point scale from 0 (*I don't have any thoughts of harming myself*) to 3 (*I would kill myself if I could*)	–	x	x	x	x	x
**Intervention-related measures**											
Credibility/expectancy questionnaire^Q^	(68)	Treatment expectancy and rationale credibility	6	Expectancy; Credibility	9-point Likert scale from 1 (*not at all*) to 9 (*very*) and 11-point Likert scale from 0 to 100%	0.84–0.85		x		x	x
Technology affinity questionnaire^g^^,^^Q^	(69)	Technological affinity	19	Excitement; positive consequences; negative consequences; competence	5-point Likert scale from 0 (*not at all true*) to 4 (*exactly true*)	0.73–0.86	x			x	x
Adverse events^Q^	Adapted from (70)	Adverse events due to intervention	3	−	Yes/no; 4-point Likert scale from 0 *(not at all)* to 3 *(very strongly)*	−			x	x	x
Client satisfaction questionnaire, adapted for inpatient fields of work^h^^,^^Q^	(71)	Patient satisfaction	8	−	4-point Likert scale with scale content depending on the item [e.g., 1 (*excellent*) to 4 (*bad*)]	0.87–0.93			x	x	
Message credibility scale^Q^	(72, 73)	Program and therapist credibility	3	−	7-point Likert scale from 1 (*very badly*) to 7 (*very well*)	0.87			x	x	
Working alliance inventory—short revised^Q^	(74–76)	Therapeutic alliance	12	–	5-point Likert scale from 1 (*rarely*) to 5 (*always*)	0.81–0.91			x	x	

Q *Self-report Questionnaire*;

I *Semi-structured Interview*;

*^a−h^Translated from German-language original*:

a *Fragebogen Körperdysmorpher Kognitionen*;

b *Fragebogen zum Körperbild*;

c *Diagnostisches Kurzinterview bei psychischen Störungen*;

d *Fragebogen zu sozialer Angst und sozialen Kompetenzdefiziten – Version für Jugendliche*;

e *Ruminations-Suppressions-Fragebogen*;

f *Fragebogen zur Erfassung der Technikaffinität*;

g *Fragebogen zur Lebensqualität von Kindern und Jugendlichen − Revidierte Form*;

h *Fragebogen zur Messung der Patientenzufriedenheit*;

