### Safety Management

Given the high suicidality in BDD (19), we aim to provide a thorough safety management in our study. First, potential participants with concrete suicidal intentions and plans identified during screening and/or diagnostic sessions will be excluded from participation and will be informed about potential places to seek treatment in their area of residence. During the intervention, we will have a weekly monitoring of suicidal ideation in place, which the study therapist has to consult prior to interaction with the patient. If suicidal ideation develops, a stepped-care plan will be set in motion, including anti-suicide contracts, a telephone call with the study therapist in which a stepped emergency plan is developed, a telephone call with the supervisor (AH; a clinical psychologist with expertise in treatment of BDD), and involvement of treatment providers in the patient's area of residence. In order to track the general development of all patients, a fortnightly supervision session will be held. The supervisor will be accessible for the study therapist during the whole project. For *post-hoc* analyses, we will also assess adverse events during and after the intervention (see measures) to assess its moderation of treatment effects.

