**Post−session:**
*after every completed session of the ImaginYouth condition and simultaneously in the Online supportive therapy condition/every week*;

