### Sample Size Calculation

Our a priori power analysis using G^*^Power (78) focused on the main hypothesis of a greater reduction of BDD symptoms in the main outcome measure from pre- to post-intervention in the ImaginYouth than in the SOT group. Thus, we calculated the number of participants necessary to test the interaction effect in a 2 (intervention type) × 2 (repeated measures assessment point) analysis of variance.

The power analysis was based on α= 0.05 and 1-β= 0.95, and an effect size of *f* = 0.36 [yielded by a meta-analysis on effects in internet-based intervention studies in youth by (32)]. The resulting total sample size is *n* = 28. Taking into account expected dropouts [about 30% in internet-based studies; (79)], we aim to recruit 20 patients per study arm type.

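### The only adverse event measure the article names counts events attributed to the programme, so serious events a participant does not blame on it have no stated route into the adverse event data

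*Protocol article*

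**What the plan says.** The Safety Management section of the protocol article states that, for post-hoc analyses, "we will also assess adverse events during and after the intervention (see measures) to assess its moderation of treatment effects". The measure it points to is one row of Table 2, under the intervention-related measures. The construct is "Adverse events due to intervention". The row has three items, answered yes/no and on a 0 to 3 strength scale, at t2, t3 and t4. Its superscript is explained below the table as "Self-report Questionnaire".

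Suicidality is handled separately. Safety Management says: "During the intervention, we will have a weekly monitoring of suicidal ideation in place". Table 2 lists a single BDI-II item on "suicidal thoughts and plans" at t0 to t4 and post-session, and the footnote defines post-session as "after every completed session of the ImaginYouth condition and simultaneously in the Online supportive therapy condition/every week". Safety Management also describes a stepped-care plan and fortnightly supervision. Under Quality Management, messages are recorded.

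Blinding is described for the diagnostician only (Assessment of Eligibility and Randomization; Quality Management). The Sample Size Calculation expects about 30% dropout and plans 20 participants per arm.

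**The concern.** An adverse event is normally recorded because it happened, and its relation to the treatment is judged afterwards. Here the stated construct puts the judgement first and leaves it to the participant. This raises three problems.

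- A serious event that the participant does not connect with the programme falls outside the definition. The article itself stresses high suicidality and mortality in this disorder, so such events are foreseeable.
- Attribution can depend on the arm. ImaginYouth includes exposure and mirror exposure (Table 1). The supportive condition offers reading material and supportive messages. Participants may more readily blame distress on the first than on the second, and a comparison of attributed events would then mix harm with attribution.
- The data depend on a returned questionnaire, so the measure is silent after a participant's last one.

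At stake is whether a statement that few adverse events occurred could be interpreted, in what the article calls the first study of such an intervention in this age group.

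**Working it through.** **1. Which events have a stated route into the data?**

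- *Worsening that the participant blames on the programme:* captured by the Table 2 measure at the next of t2, t3 or t4.
- *Suicidal thoughts or plans:* captured regardless of attribution, by weekly monitoring during the intervention and by the BDI-II item in both arms.
- *Suicide attempt, self-harm or admission not blamed on the programme:* outside the stated construct. The BDI-II item may show accompanying thoughts but does not record the event. Stepped care may be activated, but the article does not say whether activations enter the data.
- *Any event after the last returned questionnaire:* not in this measure, whatever the attribution. In ImaginYouth the post-session item is tied to completed sessions. Repeated contact after non-response is described only for the supportive arm.

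**2. Attribution by arm.** Let the true event rate be p in both arms, and let a1 and a2 be the probabilities that an event is attributed to the programme in ImaginYouth and in the supportive arm. The recorded rates are p × a1 and p × a2, with ratio a1/a2. Unless a1 = a2, the arms differ on record with no difference in harm, even with complete response. The documents give no values for a1 and a2, so the size of this bias cannot be stated.

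**3. Missing late data.** Inputs from the Sample Size Calculation: 28 needed, about 30% dropout, 20 per arm.

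- The plan's own figure reproduces: 28 / (1 − 0.30) = 40.
- Expected dropouts: 0.30 × 40 = 12, leaving 28. With equal dropout (an assumption), 14 per arm.
- One-sided 95% upper bound with zero events: 1 − 0.05^(1/n).
  - Per arm: n = 20 gives 13.9%; n = 14 gives 19.3%.
  - Both arms together: n = 40 gives 7.2%; n = 28 gives 10.1%.
  - Extreme case, all 12 in one arm: n = 8 gives 1 − 0.05^(1/8) = 31.2% in that arm, against 13.9% in the other.
- Chance of seeing at least one event in an arm: 1 − (1 − p)^n, for assumed true rates p.

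| p | n = 20 | n = 14 |
|---|---|---|
| 2% | 33.2% | 24.6% |
| 5% | 64.2% | 51.2% |
| 10% | 87.8% | 77.1% |

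These figures apply only to events within the construct, and only if those without data have the same risk as those with data. If some leave because of harm, the bounds are too low.

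**The case against.** The case on the other side has real weight.

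- *The main foreseeable risk is tracked without attribution.* Weekly monitoring, the BDI-II item in both arms, stepped care and fortnightly supervision all operate whatever the participant blames. This stands, but it covers thoughts and plans. It does not make an attempt or an admission an item of adverse event data.
- *The item wording is not shown.* Only the construct label is visible. Three items with a yes/no part and a strength scale might already separate occurrence from relation. This stands, and it is why the fix allows for correcting the label alone.
- *A condensed article need not describe a serious event log.* The full protocol may contain one. This stands too. The point rests on the definition that the article does state, not on the absence of a log.
- *The stated use is post-hoc moderation.* For that purpose an intervention-related construct is coherent, and the article does not call this questionnaire its sole safety report. It is nevertheless the only measure to which Safety Management refers for adverse events.

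A reader might also infer that serious events will go unrecorded altogether, or that every event among the expected 30% dropouts is lost. The documents support neither. Recorded messages and weekly scores may hold traces of such events. Someone who leaves after mid-intervention can already have answered at t2, and weekly or post-session items run until a participant stops. The article does not say whether the 30% leave the programme or the assessments, and a person who leaves only the programme may still answer at t3 and t4.

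**Conclusion.** The point holds in limited form. As stated, the adverse event construct is restricted to events attributed to the intervention, reported by participants who are not described as blinded. Serious events not so attributed have no stated route into the adverse event data, and the restriction can distort a comparison between arms. Suicidality monitoring mitigates this but does not close the gap.

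The loss of late data is a secondary matter. Twelve of 40 is the upper limit at 30% dropout, reached only if every dropout also stops returning questionnaires. The rise in the per-arm bound from 13.9% to 19.3% assumes that, together with equal dropout and zero recorded events. The size of any attribution bias cannot be derived from the documents.

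The change should be made, because it decides whether the adverse event results can be interpreted. It does not affect the primary efficacy analysis.

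**What to change.** 1. Define the Table 2 construct as any adverse event regardless of cause, and ask about perceived relation to the programme as a separate question. If the items already work this way, correct only the label.
2. Tabulate by arm, with all randomised as the denominator and the number with data at each time point shown, the questionnaire reports together with events the team already learns of through recorded messages, supervision and stepped-care activations. If the full protocol has an event log, cite it and use it as the source for those events.

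This concerns recording and reporting only; the clinical response to suicidality is not touched.

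The cost is the rewording of up to three items, a log built from existing records, and one table. The downsides are that more unrelated minor events will be recorded, and that the items will depart slightly from the questionnaire they were adapted from.

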**Post−session:**
*after every completed session of the ImaginYouth condition and simultaneously in the Online supportive therapy condition/every week*;

**Post−module:**
*after every completed module of the ImaginYouth condition and simultaneously in the Online supportive therapy condition; t0 = self-report screening, t1 diagnostic inteview (baseline), t2 = self-report assessment (mid-intervention), t3 = diagnostic Interview and self-report assessment (post-Intervention), self-report assessment (follow-up)*.

#### Feasibility and Acceptability Outcomes

Feasibility and acceptability will be measured using the instruments highlighted in dark gray in Table 2.

### Statistical Methods

All statistical analyses will be conducted using SPSS Statistics (IBM; Armonk, New York, USA) and R (77). Data will be mainly analyzed on an intention-to-treat basis including all randomized participants irrespective of their completion of the intervention. Additionally, study completer analyses including only participants who completed the post-intervention questionnaire battery and interviews will be conducted. Missing data will be imputed. Dropouts and completers will be compared with respect to study variables.

The main analysis focusing on efficacy of ImaginYouth will be analyzed using a repeated measures analysis of variance (rmANOVA) comparing pre- to post- intervention scores of the primary outcome. For the main analysis focusing on superiority of ImaginYouth over the SOT intervention, we will conduct a rmANOVA in the primary outcome between the two intervention conditions and changes from pre- to post-intervention. *Post-hoc t*-tests will be used to examine main effects or interactions in more detail. Cohen's d will be reported as a measure of effect size.

Secondary analyses include the examination of categorical hypotheses [e.g., for the examination of differences between ImaginYouth and SOT in responder (defined as an empirically derived cut-off point of ≥30% reduction from baseline on the BDD-YBOCS), and remission rates (operationalized as a BDD-YBOCS score ≤16 (42))] at post-intervention using Fisher's exact test. Hypotheses on efficacy and superiority regarding self-reported BDD-symptoms severity and associated (comorbid) symptoms will also be tested rmANOVAs (see above). Stability over the follow-up period and differences therein between ImaginYouth and SOT will be tested using a rmANOVA comparing pre-intervention to follow-up scores of self-reported BDD symptom severity. Finally, to examine the feasibility and acceptability of the intervention, the respective measures will be inspected descriptively.

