## Aims of the Study

The main aim of this study is to evaluate the efficacy of an internet-based therapist-guided CBT intervention (ImaginYouth) for reducing symptoms of BDD in adolescents and young adults (in the following named adolescents) and to evaluate its superiority over a supportive online therapy condition (SOT) from pre- to post-intervention. Furthermore, we aim to assess the stability of both efficacy and superiority to follow-up, and the acceptability and feasibility of the intervention format.

We hypothesize that the ImaginYouth intervention will reduce primary expert-rated BDD symptom severity from pre- to post-intervention. Further, we expect the reduction of primary BDD symptom severity to be greater in the ImaginYouth than in the SOT intervention group from pre- to post-intervention. Secondary analyses include the testing of the above-mentioned hypotheses regarding self-reported BDD-symptom severity and associated (comorbid) symptoms. Additionally, we hypothesize that the number of remitted patients and responders will be higher at post-intervention in the ImaginYouth than in the SOT intervention group. Moreover, we expect both the changes and differences between the conditions at post-intervention to be stable over the 4-week follow-up period, and thus hypothesize a significant symptom reduction from pre-intervention to follow-up and a larger symptom reduction from pre-intervention to follow-up in the ImaginYouth compared to the SOT intervention.

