## Discussion

The aim of this two-arm randomized controlled trial is to evaluate the efficacy of an internet-based therapist-guided CBT intervention (ImaginYouth) and its superiority over SOT for BDD in adolescents. Furthermore, we aim to assess the stability in terms of both efficacy and superiority over a period of 4 weeks post-intervention, as well as the acceptability and feasibility of the intervention format. It is hypothesized that ImaginYouth will reduce primary and secondary BDD symptoms from pre- to mid-, post-, and follow-up assessments. We further expect the reduction of primary and secondary BDD symptoms to be larger in the ImaginYouth group compared to the SOT group from pre- to mid-, post-, and follow-up assessment. Additionally, we hypothesize that the number of remitted patients and repsonders at post-assessment will be higher in the ImaginYouth than in the SOT intervention group.

ImaginYouth provides participants with a CBT-based intervention which makes use of techniques that are currently the first-line treatment recommended in adults (80, 81) and have shown first efficacy in youth as well (82). The ImaginYouth intervention removes some of the treatment barriers which young individuals with BDD might face. Particularly, it might not involve as many feelings of shame. Even though participation is not completely anonymous, contact with study staff (diagnostician and study therapist) do not need to involve personal face-to-face contact. We nevertheless decided in favor of a therapist-guided intervention as guidance has also been shown to increase adherence rates in internet-based interventions (83). ImaginYouth consists of interventions on cognitive, emotional, and behavioral levels, as do treatment manuals for BDD (34, 35). Thus, effects of the intervention should be perceived and measured on all levels (see secondary measures). Moreover, as previous online CBT interventions in BDD have shown (33), effects can also be measured with regard to comorbid psychopathology (e.g., a decrease in depressive symptoms as a consequence of reduced social withdrawal or cognitive restructuring of negative thoughts).

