The current design has several advantages and disadvantages. We decided in favor of an older adolescent sample mainly in order to test the intervention in individuals who are able to participate in the trial independently of their caregivers and of their own volition, in order again to limit feelings of shame when having to ask caregivers for permission. Nevertheless, in the future, the intervention could be adapted for younger adolescents and children and also expanded to be suitable for caregivers. Furthermore, we chose a randomized controlled design with an active instead of a waitlist control group, which has the advantage that we will be able to closely monitor and attend to participants in the control group. This is important as, like in other internet- and mobile-based interventions, safety management is difficult to perform, and we have tried to combat this by preparing a multilevel anti-suicidality approach. Another advantage is that participants in SOT will already receive some help that might lead to improvement, allowing unspecific working mechanisms to be controlled for. While we cannot assess long-term stability with the current design with a follow-up period of 4 weeks, the aim of the study is to assess, for the first time, the short-term efficacy in youth with BDD and to allow participants in the SOT condition to cross over to the ImaginYouth condition swiftly. Furthermore, we decided in favor of non-standardized messages after each session of ImaginYouth (and during the SOT) by the therapist, with the therapist instead adapting her comments to the patients. While this might limit generalizability, it might on the other hand decrease dropouts. And lastly, video but not audio recording during the diagnostic sessions will be non-mandatory, as this might hinder potential patients from participating. Thus, we cannot use this option to completely rule out any objective facial flaws in appearance (if other flaws are primary video recording would not be helpful anyway).

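### A main analysis of efficacy rests on ImaginYouth's own pre-post change, without the control arm that the trial includes to account for non-specific improvement

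*Protocol article*

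**What the plan says.** Statistical Methods sets out two main analyses of the BDD-YBOCS. For efficacy: "The main analysis focusing on efficacy of ImaginYouth will be analyzed using a repeated measures analysis of variance (rmANOVA) comparing pre- to post- intervention" scores. For superiority: "we will conduct a rmANOVA in the primary outcome between the two intervention conditions and changes from pre- to post-intervention".

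The same split appears elsewhere in the article. Aims of the Study states the efficacy hypothesis with no comparator: "We hypothesize that the ImaginYouth intervention will reduce primary expert-rated BDD symptom severity from pre- to post-intervention". It then adds the comparative one: "we expect the reduction of primary BDD symptom severity to be greater in the ImaginYouth than in the SOT intervention group". The Discussion opens by giving the aim as "to evaluate the efficacy of an internet-based therapist-guided CBT intervention (ImaginYouth) and its superiority over SOT for BDD in adolescents". Statistical Methods carries the efficacy and superiority pairing over to the self-reported outcomes, and the Aims carry it to follow-up.

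Two other places point the other way. Sample Size Calculation presents the greater reduction in ImaginYouth than in SOT as the main hypothesis and sizes the trial on the 2 × 2 interaction alone. The Discussion defends the active control on the ground that "participants in SOT will already receive some help that might lead to improvement, allowing unspecific working mechanisms to be controlled for".

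**The concern.** A pre-post comparison in one arm measures everything that happened between the two interviews: any specific effect of the programme, but also natural course, therapist attention, repeated interviewing and some regression to the mean. The SOT arm exists to separate the first from the rest, and the efficacy analysis does not use it. If the first analysis is instead read as a time effect pooled over both arms, it still contains no between-arm contrast.

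What is at stake is the conclusion. A trial in which both arms improve equally could report a significant main analysis labelled efficacy next to a non-significant superiority result. Readers would take the first as a finding of a randomised trial, although randomisation contributes nothing to it. No section makes an efficacy conclusion depend on the between-arm test.

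**Working it through.** **1. The plan's own figure.** Inputs from Sample Size Calculation: "The power analysis was based on α= 0.05 and 1-β= 0.95" and "an effect size of *f* = 0.36", with two groups and two occasions. The correlation between occasions is not stated, so ρ = 0.5 is assumed. For the within-between interaction, λ = f²·N·m/(1−ρ), with df 1 and N−2.

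- N = 28: λ = 0.36² × 28 × 2/0.5 = 14.52, power 0.956.
- N = 26: λ = 0.36² × 26 × 2/0.5 = 13.48, power 0.941.

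The smallest even N is 28, as stated. With 30% dropout, 28/0.70 = 40, or 20 per arm. The plan's figure is reproduced, and it belongs to the between-arm test only.

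**2. What the within-arm test detects.** With two occasions and one arm, the rmANOVA is a paired t-test. Its noncentrality is dz·√n, where dz = d/√(2(1−ρ)) and d is the mean change in SD units. At ρ = 0.5 the denominator is 1, so dz = d.

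Assume no specific effect, and the same non-specific improvement in both arms. The documents give no size for that improvement, so dz runs from 0 to 0.8. The test is taken as two-sided at 0.05 for illustration. The arm size is 20 (all randomised) or 14 (28/2, after the expected dropout). For example, dz = 0.5 and n = 20 gives noncentrality 0.5 × √20 = 2.24 and probability 0.564.

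| Shared non-specific change (dz) | Significant pre-post improvement, n = 14 | n = 20 | Between-arm test favours ImaginYouth (both n) |
|---|---|---|---|
| 0 | 2.5% | 2.5% | about 2.5% |
| 0.3 | 18% | 25% | about 2.5% |
| 0.5 | 41% | 56% | about 2.5% |
| 0.8 | 79% | 92% | about 2.5% |

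The pre-post columns come from the noncentral t distribution. The last column comes from 100,000 simulated trials per setting, which also reproduced the pre-post columns.

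**3. How often the two main analyses would part.** In the same simulations, a significant pre-post improvement without a between-arm result favouring ImaginYouth occurred in the following share of trials (n = 14 / n = 20):

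- dz = 0: 1.6% / 1.6%
- dz = 0.3: 16% / 22%
- dz = 0.5: 39% / 54%
- dz = 0.8: 77% / 90%

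**4. Dependence on ρ.** The same raw change maps to a different dz under another correlation. For d = 0.5, ρ = 0.3 gives dz = 0.5/√1.4 = 0.42, and ρ = 0.7 gives dz = 0.5/√0.6 = 0.65. For comparison, dz = 0.4 gives 28% / 40% and dz = 0.6 gives 55% / 72% (n = 14 / n = 20).

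**The case against.** The strongest reply is that the right hierarchy is already in the document. The between-arm comparison is a main analysis, it is the one called the main hypothesis, and it alone determines the sample size. That stands, and it limits the fault to the status and label given to the pre-post analysis. It does not remove the fault, because the Aims, Statistical Methods and the Discussion all keep efficacy as a separate claim with its own test. Nor is this a detail left to an analysis plan: the article names the test.

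It is also fair to say that the percentages above are not inflated type I error. If both arms really improve, the within-arm null hypothesis is false and the test is right to reject it. Only the attribution to the programme would be wrong. How often that happens depends on an assumed quantity, and at zero non-specific change nothing is lost.

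Some stronger readings are tempting but go beyond the text:

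- **That a significant pre-post test would make the trial positive, or that the plan gives two chances of success at 0.05 each.** No success rule is stated, and α = 0.05 appears only in the power calculation for the interaction.
- **That the superiority test is underpowered, so the split result is the likely one.** Under the stated inputs and ρ = 0.5, power is 0.956 with 28 patients. The required N does vary with the unstated correlation (54 at ρ = 0, 38 at 0.3, 18 at 0.7), but that does not show a shortfall.
- **That the post-hoc t-tests compare significance arm by arm.** The text says only that they will explore main effects or interactions, which could equally mean between-arm tests.
- **That regression to the mean must be large.** The numerical entry cut-off is on the self-reported BDDI at screening. The primary outcome is a different, expert-rated scale first measured at baseline, with no entry threshold of its own. Some regression remains plausible, but it is attenuated.
- **That follow-up is assessed without a comparator.** Statistical Methods also plans to test differences between the arms there.

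**Conclusion.** The point holds as an inconsistency between the claim and the test. An uncontrolled pre-post change is designated a main analysis of efficacy in a trial whose own sample-size and design rationale rest on the between-arm comparison. A significant result from it would not show that ImaginYouth works.

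The size of the risk is conditional. With no specific effect and ρ = 0.5, it runs from 2.5% when there is no non-specific change to 79% (n = 14) or 92% (n = 20) at 0.8 SD. A moderate change of 0.5 SD gives 41% to 56%. The documents make some non-specific change plausible, since both arms receive therapist contact and the Discussion itself says that support may lead to improvement, but they do not quantify it. The sample size is not in dispute here.

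**What to change.** In Aims of the Study, Statistical Methods and the opening of the Discussion:

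1. Make the between-arm contrast in BDD-YBOCS change from baseline to post-intervention the sole confirmatory test of efficacy, in line with Sample Size Calculation.
2. Present pre-post and pre-to-follow-up change within each arm, including the self-reported outcomes, as descriptive estimates with 95% confidence intervals.
3. State that no efficacy claim rests on within-arm change.

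The cost is rewording only. No new data or patients are needed: 28 evaluable patients (40 recruited) already match the plan's target for the between-arm test under its stated inputs and ρ = 0.5. The chance of a false finding in favour of ImaginYouth on that test stays at about 2.5% whatever the shared non-specific change.
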